## Abstract

**Background:**

Requirements for frequent dispensing of antiretroviral therapy (ART) place demands on health systems and can lead to suboptimal adherence and disengagement in care for patients due to the time and cost of frequent clinic visits. Rigorous data are needed to define optimal ART dispensing strategies and to evaluate the impact of a longer medication supply on retention and virologic suppression and determine whether this strategy lowers costs for both the patient and the health system. To date, no randomized studies have tested the benefits of 6-month dispensing of ART compared to 3-month and standard of care approaches.

**Methods:**

This study will be an unblinded cluster-randomized, matched controlled trial conducted among 8200 stable, HIV-infected individuals age 18 years and older on ART in Malawi and Zambia, to compare three ART dispensing intervals on the outcomes of retention in care (primary outcome), virologic suppression, and cost-effectiveness. Thirty clusters will be matched according to country, facility type, and ART cohort size and randomized to one of three study arms: standard of care, 3-month dispensing, and 6-month dispensing. Study participants will be followed, and outcomes will be measured at 12, 24, and 36 months. A subset of participants (n = 240) and providers (n = 180) will also participate in qualitative interviews to evaluate feasibility and acceptability of different ART dispensing intervals.

**Discussion:**

This study will be the first to compare 6-month and 3-month ART dispensing intervals for stable, HIV-infected individuals in Malawi and Zambia. We focus on outcomes relevant to country programs, including retention, virologic suppression, and cost-effectiveness. Results from the study will help resource-limited health systems better understand the full scope of outcomes resulting from various ART dispensing intervals and help to inform health policy decisions.

**Trial Registration:**

ClinicalTrials.gov, NCT03101592. Registered on 18 March 2017.

Pan African Clinical Trials, PACTR201706002336105. Registered on 2 June 2017.

**Electronic supplementary material:**

The online version of this article (doi:10.1186/s13063-017-2177-z) contains supplementary material, which is available to authorized users.

## Background

The 2015, the World Health Organization (WHO), the Joint United Nations Program on HIV/AIDS (UNAIDS), and the U.S. President’s Emergency Plan for AIDS Research (PEPFAR) all announced their support for global HIV control targets known as “90-90-90” [1, 2]. The goals of 90-90-90 are to identify 90% of people living with HIV, initiate 90% of HIV-diagnosed individuals on ART, and achieve viral suppression in 90% of those on ART. Modeling has indicated that achieving the 90-90-90 targets will require most low-income and middle-income countries to increase sharply the number of patients successfully retained on lifelong ART, with major implications for the resource requirements and costs of national treatment programs, and will heighten the challenge of maintaining program quality and improving patient outcomes as access expands.

Barriers to achieving the “third 90”—long-term viral suppression—include sub-optimal adherence and retention in care. For patients in sub-Saharan Africa, reasons for these poor outcomes have included the requirement for frequent clinic visits to receive medication refills, long wait times in ART clinics, high costs for travel to clinics, missed wages, and life events that lead to missed clinic visits [3–6]. Data from Zambia, a country with lower-middle income and high HIV prevalence in southern Africa, for example, suggest that requirements for monthly dispensing and/or guidelines that require multiple separate visits for refills and clinician evaluation impose a large burden on individuals living with HIV, which can in turn lead to treatment interruptions or complete disengagement from care [7].

One potential solution to this problem is to increase dispensing intervals to as long as 6 months to reduce patients’ visits to the clinic. An observational analysis of 130,000 patients in Zambia showed that patients on a 6-monthly appointment schedule were less likely than those on a monthly schedule to have gaps in medication refills (adjusted odds ratio (aOR) 0.50, 95% confidence interval (CI) 0.43–0.57) or be lost to follow up (aOR 0.48, 95% CI 0.40–0.59) [8]. Extension of refill intervals has been employed in many high-resource settings, including the USA, with supply provided up to every 6 months for stable patients [9, 10]. Potential benefits of multi-month dispensing may include improved adherence to ART, improved retention in care, and decongestion of clinics, which allows staff to focus on the sick, allows the clinic to initiate more new patients on ART, improves operational efficiency at clinics, and reduces costs of providing and obtaining ART.

Although the evidence from Zambia cited above is promising, it reflects the fact that longer dispensing intervals were almost certainly assigned to the patients with the best adherence records, and thus cannot tell us how multi-month dispensing affects outcomes. A review of the literature reveals no randomized studies of ART dispensing intervals in resource-limited settings and no cost estimates from real-world settings. Rigorous data are needed to define optimal dispensing strategies and to determine whether longer drug supply intervals result in improved outcomes and/or lower costs for both the patient and the health system.

The main objective of the INTERVAL study, a PEPFAR/US Agency for International Development (USAID)-supported, multi-site cluster-randomized trial, is to compare standard of care to 3-month and 6-month ART dispensing. The primary outcomes to be studied are retention in care at 12, 24, and 36 months. We will also evaluate secondary outcomes of virologic suppression and cost-effectiveness at these same time points. INTERVAL will contribute to the limited body of knowledge on multi-month dispensing of ART in resource-limited settings and may be used to better define best practices for cost-effective ART programs in Malawi, Zambia, and similar settings.

## Methods/design

INTERVAL will be a pragmatic, cluster-randomized, non-blinded, non-inferiority trial conducted at 30 health facilities in Malawi and Zambia. It will compare three ART dispensing strategies for stable patients – (1) standard of care, (2) 3-month ART dispensing, and (3) 6-month ART dispensing – on retention in care in Malawi and Zambia.

The study protocol was developed using the SPIRIT (Standard Protocol Items: Recommendations for Interventional Trials) Checklist (see Additional file 1) and adheres to the SPIRIT recommendations. The protocol has been approved by the institutional review board of the University of California, Los Angeles (UCLA), the National Health Sciences Research Council (NHSRC) in Malawi, the Zambia Excellence in Research Ethics and Science (ERES) Converge, the Zambia National Health Research Board (ZNHRB), and the Zambia Medicines Regulatory Authority (ZAMRA). The trial is registered with ClinicalTrials.gov as NCT03101592.

### Intervention

This study will compare standard of care to two alternative dispensing strategies. Under standard of care, ART dispensing intervals are based on provider opinion. Malawi and Zambia ART guidelines recommend 3-month dispensing for stable patients, but adherence to guidelines is variable and dispensing may vary due to provider and/or patient preference or medication availability. Participants in the 3-month dispensing study arm will receive a 90-day supply of ART and will have routine clinic visits every 90 days. Participants in the 6-month dispensing study arm will receive a 180-day supply of ART and will have routine clinic visits every 180 days. For all arms, other HIV services will be standard of care and supplies of co-trimoxazole (CPT) and isoniazid (IPT) will also be provided based on the assigned ART dispensing interval and country-specific guidelines about use of these therapies as part of routine HIV care.

Pharmacy support will be provided as part of the study, to ensure medication stock outs do not occur at study sites and that study sites do not take drug stocks away from non-study facilities. The trial is being conducted in close collaboration with the Ministries of Health in Malawi and Zambia and USAID, with support from the Supply Chain Management Systems (SCMS). Participants in the 6-month arm will be offered generic plastic bags to assist with carrying the large supply of medications. Participants will be given information about “ideal” basic storage conditions for medications, particularly in regard to temperature and avoidance of storage in direct sunlight. Participants who provide written informed consent will be willing to participate in any of the study arms; however, those in the 6-month arm may request a reduction in refill duration at any point during follow up. The proportion of individuals changing from 6-month ART dispensing to shorter intervals and reasons for changing will be captured during follow up.

To measure the primary outcome of retention, data will be abstracted from participants’ medical records. In Malawi and Zambia, default from care is defined as being out of ART for more than 60 days, and this definition will be used for the endpoint of retention (<60 days without ART at each time point).

Secondary study outcomes include virologic suppression, cost-effectiveness, and feasibility and acceptability to patients and to providers and will be measured at 12, 24, and 36 months. Viral load data will be obtained from medical records based on any available data recorded during the prior year. Cost-effectiveness will be analyzed from both patient and health system perspectives by surveying participants at enrollment about time and costs associated with each clinic visit and by creating inventories of all resources and costs to the facility and health system for each patient visit. Feasibility and acceptability will be measured by conducting qualitative in-depth interviews with a subset of 240 participants (120 per country) and 180 providers (90 per country) evenly balanced among the three study arms. A flowchart of the study is provided in Fig. 1. Our main hypothesis is that 6-month ART dispensing will be non-inferior to 3-month intervals for retention and virologic suppression, but that 6-month intervals will be cost-effective compared to 3-month intervals.

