#### Entry visit data collection

All patient baseline data will be collected in the entry visit, which may come immediately after screening for eligible patients, or may take place at the next visit when a viral load result is available. Two types of data will be collected at the entry visit. First, the participant’s medical record will be reviewed to collect clinical history, including date of HIV diagnosis, date of ART initiation, use of CPT and/or IPT, and history of ART clinic visits and ART dispensing intervals in the prior 12 months. The second type of data will come from an interview with the patient. In the interview, the study interviewer will obtain sociodemographic information about the participant, including gender, highest level of education, household composition, employment status, HIV disclosure status, and travel and opportunity costs related to the participant’s ART clinic visits. After completion of the entry visit data collection, the participant will complete her or his routine clinic visit with site providers and receive ART dispensing as per the site randomization. If CPT and/or IPT dispensing is standard of care for the facility, CPT and/or IPT will also be provided as per the randomized dispensing interval.

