#### Follow-up data collection

Retention and virologic suppression will be assessed 12, 24, and 36 months after the entry visit date. At each of these time points, data from participants’ medical records will be collected by study staff. Data will include number, timing, and reason for clinic visits, retention in care (and if not retained, reason), possession of ART based on number of pills dispensed at each visit, possession of CPT and/or IPT based on number of pills dispensed at each visit, and viral load. Study staff will allow up to 60 days after a time point has been reached before medical record review, allowing for participants to meet the protocol-defined definition of default. For participants who default, facility standard of care procedures for tracing may be used, but the study will not make contact with the participant for the purposes of facilitating return to care.

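### Retention is scored from ART supply, but the scoring date is not fixed: at most permitted dates the same disengagement counts as failure under 3-month and retention under 6-month dispensing.

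*Protocol article*

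**What the plan says.** All references are to the protocol article.

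- **Outcome.** Under Intervention, a gap in ART supply of over 60 days counts as default, following the two countries' practice. The outcome rule is taken from it: "this definition will be used for the endpoint of retention (<60 days without ART at each time point".
- **Data.** Under Follow-up data collection, the abstracted items include "possession of ART based on number of pills dispensed at each visit".
- **Dispensing.** The first supply is given at entry, when participants "receive ART dispensing as per the site randomization". After that the 3-month arm "will receive a 90-day supply of ART and will have routine clinic visits every 90 days" and the 6-month arm "will receive a 180-day supply of ART and will have routine clinic visits every 180 days".
- **Review date.** "Study staff will allow up to 60 days after a time point has been reached before medical record review", with the stated purpose of "allowing for participants to meet the protocol-defined definition of default".
- **Comparison.** The main hypothesis, at the end of the Intervention section, is non-inferiority of 6-month to 3-month dispensing. The Primary outcome section also compares each intervention arm with standard of care. The Sample size section gives 5% failure under standard of care and 7.5% as the limit, an implied margin of 2.5 percentage points.

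The article does not say whether the gap is measured at month 12 itself or at the date of record review. It does not require review to wait the full 60 days.

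**The concern.** The endpoint depends on when the pills run out, and the number of pills handed over per visit is the randomised factor. A longer supply delays the day on which someone who has stopped attending can be seen to have stopped. If the scoring date falls before that day in one arm and after it in the other, identical behaviour is recorded as different outcomes.

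In a superiority trial this would be a bias to describe. In a non-inferiority trial, an artefact in favour of the 6-month arm acts directly on the error that matters most: declaring 6-month dispensing non-inferior when it is not.

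**Working it through.** **1. The plan's own sample size.** Inputs: 5% failure, margin 0.025, one-sided 0.05, power 90%, ICC 0.004, 10 clusters per arm.

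- Individually randomised n = (2 × 0.05 × 0.95)(1.645 + 1.282)² / 0.025² = 1301.7 per arm.
- With k = 10 clusters, m = n(1 − ICC)/(k − n × ICC) = 1301.7 × 0.996/(10 − 5.207) = 270.5, rounded up to 271 per cluster, 2710 per arm and 8130 in total.

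This agrees with the article. The sample size is not at fault, and the margin of 2.5 points is confirmed.

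**2. Who can be in default, by scoring date.** Take month 12 as day 365 and assume on-schedule visits. Supplies run out at days 90, 180, 270 and 360 in the 3-month arm and at days 180 and 360 in the 6-month arm. Default on scoring day D needs run-out before day D − 60.

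| Scoring day D | Run-out must precede | Latest missed refill that counts, 3-month | Latest missed refill that counts, 6-month |
|---|---|---|---|
| 365 | 305 | day 270 | day 180 |
| 420 | 360 | day 270 | day 180 |
| 425 | 365 | day 360 | day 360 |

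The pattern at day 365 holds up to day 420. On day 420 itself a run-out at day 360 gives a gap of exactly 60 days, which is neither more than 60 (default) nor under 60 (retained). Only the last five days of the permitted review period treat the two arms alike.

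**3. Size when scored from day 365 to day 420.** Assumption, not a document figure: 5% leave care per year at a constant rate, equally in both arms. The probability of leaving by day x is 1 − 0.95^(x/365).

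- 3-month arm: 1 − 0.95^(270/365) = 3.7%.
- 6-month arm: 1 − 0.95^(180/365) = 2.5%.
- Difference 1.2 points; 1.2/2.5 is about half the margin.
- If the 5% is instead reached by day 270: 0.95^(180/270) − 0.95 = 1.6 points, about two thirds of the margin.
- A standard-of-care patient supplied monthly, scored at day 365: 1 − 0.95^(300/365) = 4.1%, which is 1.6 points above the 6-month arm. Monthly supply is also an assumption; the article says guidelines recommend 3-month dispensing for stable patients.

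**4. Size when scored at day 425.** With on-time refills both arms give 1 − 0.95^(360/365) = 4.9%, a difference of 0. Lateness changes this because the slack is only 365 − 360 = 5 days. Simulating one million participants per interval, with the same exit rate and assumed lateness, gives these differences (positive favours 6-month):

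| Refill lateness | Difference, points |
|---|---|
| on time | 0.0 |
| 7 days early to 7 late, uniform | −0.2 |
| 0 to 7 days, uniform | −0.4 |
| 0 to 14 days, uniform | +0.5 |
| 0 to 30 days, uniform | +1.2 |

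Small delays add up over three 3-month refills and hide exits there first, so the sign is negative. Larger delays push the last run-out past day 365 in both arms. The 6-month arm then falls back to the day-180 refill and the 3-month arm only to the day-270 refill, so the sign turns positive.

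**5. Effect on the non-inferiority error.** Apply the 2.5-point margin to 6-month versus 3-month. Design effect = 1 + 270 × 0.004 = 2.08. At true failure of 5% and 7.5%, SE = √[2.08 × (0.05 × 0.95 + 0.075 × 0.925)/2710] = 0.00947. A 1.2-point shift gives 1 − Φ(1.645 − 0.012/0.00947) = 35% instead of 5%. Taking the SE at the shifted rates gives 39% for a 1.23-point shift and 40% for 1.25 points.

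**The case against.** The strongest reply is that the review delay exists for this purpose. Its stated aim is to let participants reach the default definition, which makes little sense if the gap is frozen at month 12. If review always waits to day 425 and refills are on time, the two fixed arms are scored identically. A reader might infer from the day-365 arithmetic that a bias of half the margin is built into the endpoint, or that a 6-month participant always needs one return visit and a 3-month participant three. The documents support neither. Both depend on scoring by day 420. The visit count also assumes on-schedule visits: at day 365 any 3-month dispensing after day 215 (305 − 90) counts as retained, however many returns preceded it. With small lateness at day 425 the difference goes against the 6-month arm, which is conservative for non-inferiority. This part of the reply stands and limits the finding.

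Three further replies stand only in part:

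- *Reasons for non-retention are also abstracted.* Recorded transfers or deaths need not wait for run-out, so the calculation applies to silent disengagement.
- *The definition is the national one, in a pragmatic trial, and longer possession is part of what 6-month dispensing does.* That is a fair choice of target, and the 60-day rule need not change. It does not explain why the result should depend on the day the record is read.
- *An article may leave the scoring date to the full protocol or SAP.* A clarification there could settle it. But the supply-based definition and the upper limit on the review delay are both stated here, and together they permit the problem.

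**Conclusion.** The point holds in limited form. The endpoint definition and the record-review rule together do not guarantee that equal disengagement gives equal measured failure. Scored anywhere from day 365 to day 420, with on-schedule visits and an assumed constant 5% per year exit, the 6-month arm gains about 1.2 points on the 3-month arm, half the 2.5-point margin. False non-inferiority at the margin then rises from 5% to about 35-40%. Scored at day 425, the difference is 0 with on-time refills and about −0.4 to +1.2 points over the lateness patterns tried.

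The bias is therefore possible rather than certain, and its size and sign depend on the scoring date and on refill lateness. The article gives neither lateness nor the timing of exits. It matters because the less favourable scoring dates make up nearly all of the permitted period, and the favourable case has only five days of slack.

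**What to change.** - **Outcome wording.** Keep the 60-day default definition. Score each time point on a calendar window common to all three arms: for example, whether ART was collected in the window and within 60 days after run-out of the last supply collected before the window opened.
- **Where the window opens.** It must suit standard of care too. If it opens at day 330, an on-time monthly patient qualifies at day 330 and the fixed arms at day 360. Measured failure is then 1 − 0.95^(330/365) = 4.5% against 4.9%, an artefact of about 0.4 points against both intervention arms. If it opens between days 330 and 360, for example at day 345, the last earlier supply of an on-time patient runs out at day 360 under monthly, 3-month or 6-month dispensing, and all give 4.9%.
- **Record review.** Replace the upper limit of 60 days with a fixed minimum long enough to observe run-out plus 60 days in every arm, for example 120 days (day 485). That covers a month-6 refill collected as late as day 485 − 60 − 180 = day 245. Apply the same rule at 24 and 36 months.
- **Check.** Before data lock, simulate equal true disengagement under early, on-time and late refills, and confirm that measured failure is close to equal in all three arms.
- **The 60-day tie.** State how a gap of exactly 60 days is classified.

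Cost: data lock about two months later at each time point (120 − 60 = 60 days), and a similar delay to any interim analysis using the outcome. No new data items are needed, because visit dates and pills dispensed are already abstracted.

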**Fig. 1 Fig1:**
[figure not shown]
Flowchart of study protocol. *See Table 1. ART antiretroviral therapy

### Study sites

The study will be conducted at 30 clusters in Malawi and Zambia. A cluster is defined as a hospital or health center that serves as an outpatient ART site. All clusters will either be government or mission facilities that provide free HIV care. Clusters will be selected based on ART cohort size and ability to enroll at least 271 participants, ability to perform viral load testing as part of routine care, completeness of medical records, and willingness to participate in the study. Sites in Malawi will be selected from the Central and Southern regions, and sites in Zambia will be selected from Central and Copperbelt Provinces. Sites participating in ongoing research that influences the frequency or location in which patients receive ART will be excluded, as will those that have active research underway on adherence and retention.

### Blinding and allocation

Random assignment of matched clusters will be determined by computer. Clusters will be matched based on available information that could potentially predict outcomes, including ART cohort size and region. Matched clusters will then be randomly allocated with one receiving the 3-month intervention, one the 6-month intervention, and one the control condition. Allocation will be completed by the study analyst. Clusters will then be informed of the allocation. No attempt will be made to blind the sites or patients to their allocated group, as both providers and patients will be aware of the amount of medication dispensed and the timing between appointments.

